### AIM 1. Evaluate the acceptability, frequency and timeliness of SBDOH intervention, and level of challenges of SBDOH in HIV treatment among PLWH

We hypothesize that greater than 75% of the participants in the ISS-SBDOH arm will rate the intervention as fitting their routine activities of daily life. To test this hypothesis, we will perform analyses in two levels: (1) Obtain point estimates of ratings about the intervention and conduct one group binomial test of the proportion with answers that indicates a fit (or better fit). This will be done at each of the time point of baseline, and weeks 4, 8, 12, and 16; (2) Generalized linear mixed models (GLMM) will be used to model the changes of ratings over time controlling characteristics (e.g., demographics, SBDOH, regimen type (single/multiple pill), and viral load). GLMM can model not only global fixed effects (e.g., the regimen type), but also random effects (e.g., change over time within a person). We also hypothesize that the ISS-SBDOH arm will have significantly higher frequency and better timeliness of the SBDOH intervention sessions than the UC arm; and the ISS-SBDOH arm will have lower level of challenges of SBDOH over time than the UC arm. To test this, we will use GLMM to model the number of challenges of SBDOH over time through parameter estimate of time (fix effect) in the model.

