### Randomization

Randomization will take place after the baseline assessment and before the intervention begins. The UC arm is chosen as the control condition because it meets ethical and moral requirements to attempt treatment. Eligible patients will be randomized to one of the two conditions using a stratified urn randomization procedure to increase the likelihood of balanced allocation of prognostic variables at baseline. We will stratify by two factors: (i) single/multiple tablet regimen, and (ii) detectable/undetectable viral load at baseline through a 2 × 2 factorial stratification, to assign them into intervention arm or UC arm within each of the four cells. Randomization is implemented electronically through REDCap.

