### SBDOH Intervention

Like many urban safety net HIV clinics, enrollment clinical site personnel (nurses, case workers, and social workers) can provide services for SBDOH needs by a multidisciplinary team. Figure 3 summarizes how this service can be activated in the intervention arm. In UC arm, patient identification/referral is initiated during a clinic visit, or if a patient reaches out between visits to their primary provider or a member of the multidisciplinary team. Once triggered, the team will meet with the participant to assess SBDOH and use resources and expertise available to address key issues. The team members are experienced and when appropriate can provide referrals to dedicated HIV mental health specialists. The social workers and case managers are experienced at addressing social/behavioral determinants, including but not limited to in- or out-patient substance use disorder, housing, and food insecurity. The mental health specialists are also focused on and experienced in addressing the challenges PLWH encounter, including anxiety, primary psychiatric conditions, as well as stigma and discrimination. However, this signal to address SBDOH needs often occurs weeks to months after issues have emerged. In this study, the SBDOH intervention will be triggered if a participant has missed his/her prescribed ARVs for a total of 3 days within a five-day period monitored by real-time sensor. In addition, during the first 16 weeks, the participants in the intervention group will use ID-Cap to monitor their daily HIV adherence in real-time and receive their pre- and post- dosage reminders. With 4-week intervals, we will ask participants for their feedback on ID-Cap and/or the SBDOH session, when applicable.

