## Outcomes

### Primary outcome

(i)Acceptability of the integrated intervention will be measured at baseline, and around week 4, 8, 12, and 16, evaluated by quantitative measures interviews. The items in the quantitative measure will be rated on a five-point Likert scale ranging from very strongly disagree to very strongly agree. Acceptability will be measures in terms of: overall satisfaction (would recommend to friend, would use outside of study setting, satisfied with system), utility, and specific items such as helpfulness and convenience. In addition, we will ask participants to rate items specific to the ID-Cap system (comfort of wristband, comfort receiving text messages).(ii)Frequency and timeliness of SBDOH intervention, level of challenges of SBDOH in HIV treatment will be measured at baseline, and around week 4, 8, 12, 16, 20, and 28. We will collect SBDOH measures, such as economic stability (e.g., food security), health (e.g., gap in health coverage), neighborhood and built environment (e.g. transportation needs), social and community context (e.g., violence, and criminal justice involvement), and substance and alcohol use, sexual behavior, and other health related behaviors. Challenges of SBDOH will be measured as the count of SBDOH issues one is facing, and the degree of each issue (e.g., low/medium/high with housing challenge determined by nurse or care coordinator) with summary scores. Frequency and timeliness of SBDOH intervention are measured as number of sessions, and time to first, and subsequent sessions, if applicable, from baseline, and others. This information will also be collected when intervention is triggered by the monitoring system.(iii)Adherence to ART measured by ID-Cap system for 16 weeks.(iv)Self-Reported Medication Adherence [34]. We will use a widely used measure of percent of prescribed dose taken during the preceding seven days. We will also measure patterns of dosing (e.g., patterns of consecutive missed doses in the past two weeks).

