### Sample size calculation

Sample size calculation and power analysis were conducted based on the primary and secondary end points. For Aim 1, 55 subjects to be recruited in the ISS-SBDOH arm and 55 in the UC arm enable us to obtain stable point estimates and test the hypotheses for acceptability of the intervention program using one sample binomial approach. For the frequency and timeliness of SBDOH intervention and level of challenges, group sample sizes of 55 in the ISS-SBDOH arm and 55 in the UC arm will enable us to detect a difference as small as 0.5 in a continuous outcome (a medium Cohen’s effect size) with 80% power, and a significance level of 0.05 using a two-sided two-sample t-test. For Aim 2, using repeated measures analysis with intra-subject correlation of 0.1, a type I error of 0.05, a type II error of 0.2 (or 80% power), and average number of available data points 3.5, out of 5 data points (baseline, weeks 4, 8, 12, 16), 55 subjects in each of the two arms will enable us to detect a difference as small as 0.29 in standardized unit of the outcomes (e.g., adherence to ART) between the two arms, which is statistically and clinically meaningful. For Aim 3, for the binary outcome variable of viral suppression, using repeated measures analysis with similar set-up as Aim 2, the sample size of 55 participants in each of the 2 arms will be able to detect a 9% difference (or an odds ratio of 2.7) between the 2 arms (assuming 85% viral suppression at week 16 for control arm) and this effect size is considered clinically meaningful. Thus, the planned sample size should be sufficient for the proposed analyses.

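### Acceptability is tested at baseline, before anyone is assigned to or has used the system, and then at four later visits with none named as deciding

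*Protocol article*

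**What the plan says.** All references are to the protocol article.

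- **Hypothesis (Aim 1 analysis).** It concerns the intervention arm only: "greater than 75% of the participants in the ISS-SBDOH arm will rate the intervention as fitting their routine activities of daily life".
- **Test times (Aim 1 analysis).** The one-sample binomial test is repeated: "This will be done at each of the time point of baseline, and weeks 4, 8, 12, and 16". No visit, and no rule for combining visits, is named as settling the hypothesis. Sidedness is not stated.
- **Measurement times (Primary outcome, item i).** They match the test times: "Acceptability of the integrated intervention will be measured at baseline, and around week 4, 8, 12, and 16".
- **Order of events (Randomization).** "Randomization will take place after the baseline assessment and before the intervention begins".
- **Period of use (SBDOH Intervention).** "during the first 16 weeks, the participants in the intervention group will use ID-Cap to monitor their daily HIV adherence in real-time".
- **Feedback schedule (Process measures).** Participants' feedback on ID-Cap is collected from week 4; baseline is not listed.
- **Multiplicity (Statistical analyses).** Significance is set at 0.05, and appropriate corrections, with Bonferroni as the example, are to keep the effective type I error at that level.
- **Sample size (Aim 1 part).** It cites 55 participants in each arm as enough to "test the hypotheses for acceptability of the intervention program using one sample binomial approach". It gives no alternative proportion and no power for this test.

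**The concern.** Acceptability is the first primary outcome listed. At the baseline assessment there is no ISS-SBDOH arm, and nobody has worn the reader, received a reminder or had a triggered session. Some of the listed items, such as comfort of the wristband and of receiving text messages, cannot then be answered from experience. A significant result at baseline would say that people expect to like the system. Reported under this hypothesis, it would be read as evidence that they do.

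The second problem is that one hypothesis gets five tests with no rule for mixed results. If it passes at week 4 and fails at week 16, the plan does not say whether the hypothesis is supported. A correction for five tests costs power. Counting any single success without a correction would not fit the promise to hold type I error at 0.05.

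**Working it through.** **Order of events.** The sequence is baseline assessment, then randomization, then 16 weeks of ID-Cap use in the intervention arm. A baseline rating therefore precedes both assignment and exposure. The only earlier contact with anything related is the over-encapsulated pill given to check tolerability (Schedule of events and assessments). That pill is not use of the sensor system and says nothing about fit with daily routine.

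**Inputs for the size of the multiplicity problem.**
- n = 55 in the ISS-SBDOH arm (Sample size calculation).
- Null proportion 0.75 (Aim 1 analysis).
- Overall alpha 0.05 (Statistical analyses).
- Five tests (Aim 1 analysis).
- True acceptability of 85%, 90% or 95%: an assumption, because the document gives no alternative.
- Sidedness: not stated, so both are shown.

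The document gives no critical count or power for this test, so there is no figure to reproduce.

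**Method.** The bar is the smallest r for which P(X ≥ r | 55, 0.75) is at most the allowed tail probability. Power is P(X ≥ r | 55, p1). Bonferroni allows 0.05/5 = 0.01 per test, or 0.005 in the upper tail if two-sided.

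| Plan | Allowed upper tail | Bar | Attained tail | Power at 85% / 90% / 95% |
|---|---|---|---|---|
| One test, one-sided | 0.05 | 47/55 (85.5%) | 0.0454 | 0.555 / 0.906 / 0.998 |
| Five tests, one-sided | 0.01 | 49/55 (89.1%) | 0.0080 | 0.263 / 0.690 / 0.981 |
| One test, two-sided | 0.025 | 48/55 (87.3%) | 0.0205 | 0.405 / 0.820 / 0.994 |
| Five tests, two-sided | 0.005 | 50/55 (90.9%) | 0.0027 | 0.148 / 0.524 / 0.944 |

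Power in the five-test rows is per visit.

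**Dropping baseline only.** Four tests allow 0.05/4 = 0.0125 one-sided, or 0.00625 in the upper tail. One-sided, 48/55 has tail probability 0.0205, above 0.0125, so the bar stays at 49. Two-sided, 49/55 has 0.0080, above 0.00625, so the bar stays at 50. Removing baseline corrects validity but recovers no power. Naming one deciding visit recovers it.

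**No correction, success at any visit.** For independent tests at a nominal 0.05, the type I error is 1 − 0.95^5 = 0.226 for five tests and 1 − 0.95^4 = 0.185 for four. Ratings by the same people are correlated, so the true figure would be lower.

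**Counting missing ratings as not agreeing.** Suppose 88% of raters agree (assumed) and a fraction m of the arm gives no rating. The success probability per participant becomes 0.88 × (1 − m). Against the bar of 47/55, power is 0.79 at m = 0, 0.44 at 5% (success probability 0.836), 0.16 at 10% (0.792) and 0.04 at 15% (0.748). This bears on the choice of remedy.

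**The case against.** The strongest reply has four parts.

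1. *A deciding visit is analysis-plan detail, and the article is a condensed account.* This is fair for the choice of visit. It does not cover the baseline test, which the article positively prescribes; an analysis plan could remove it only by departing from the published text.

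2. *Bonferroni is only an example and is not tied to these five tests.* This stands. A less costly correction, or a rule requiring success at every visit (which needs no correction), would also fit the text. The power loss above is what follows if Bonferroni is applied, not something the plan has fixed.

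3. *Repeated ratings are useful.* This also stands. The Study duration section gives fatigue with the sensor system as one reason for 16 weeks, so a difference between week 4 and week 16 would be informative. That supports reporting every visit, but it does not require a formal test at each.

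4. *The Aim 1 sample size sentence is only loose wording.* I agree. It mentions both arms, but the hypothesis is confined to the ISS-SBDOH arm, and nothing shows that 110 participants would enter the test.

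A reader might infer three stronger points that the document does not support. The baseline test does not itself cause the power loss, since the bar is the same with four tests as with five. The document does not show that the model of ratings over time starts at baseline: the list of visits is attached to the binomial tests, and the sentence on the mixed model names none. Nor does it show that the result will be distorted by people who stop using the system, because it gives no attrition figure for these ratings.

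**Conclusion.** The concern holds in two parts. First, the plan fixes a test of acceptability at a time when, by its own sequence, no arm exists and nobody has used the intervention; that test cannot address the hypothesis. This rests on the text alone. Second, a primary hypothesis is tested five times without a deciding visit under a promise to control type I error. If Bonferroni is applied, the bar rises by two participants, from 47 to 49 one-sided or from 48 to 50 two-sided. The loss matters most at moderate true acceptability: one-sided power drops by 0.29 at 85% (0.555 to 0.263) and by 0.22 at 90%, but by under 0.02 at 95%. These sizes assume all 55 participants give a rating, the stated true rates and an exact binomial test. The point concerns the acceptability claim only; it does not touch the adherence or viral load comparisons.

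**What to change.** - Remove baseline from the acceptability binomial tests, and from the model of ratings over time if it is included there. Alternatively, keep the baseline rating as a descriptive item labelled expected acceptability.
- Name one post-exposure visit as the deciding test and state its sidedness. Week 16, the end of the intervention, is a natural choice, though another post-exposure visit could be justified.
- Report the remaining visits as proportions with confidence intervals.
- Clarify in the Sample size calculation that only the 55 ISS-SBDOH participants inform this test.
- Do not make counting non-raters as not agreeing the primary rule, given the loss of power shown above. At most, report it as a sensitivity analysis.

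These are wording changes and need no new data. The cost is one formal acceptability claim instead of several.

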**Methods:**

In this protocol paper, we describe the design and procedures for a National Institutes of Health-funded randomized controlled trial that tests an innovative, integrated intervention combining the latest pill ingestible sensor system (the ID-Cap from etectRx) and strategies to address SBDOH. The intervention will trigger real-time actions to rapidly address SBDOH-related barriers when pre-specified patterns of poor adherence are detected (antiretroviral doses missed on three days within a five-day period). A cohort of 110 PLWH who have, or are at high risk for, sub-optimal adherence will be recruited from an HIV clinic in Los Angeles County. Participants will be randomized into the ingestible sensor intervention arm or the usual care arm. The intervention will run for 16 weeks, followed by a 12-week post-intervention period to evaluate sustainability. The primary outcomes are acceptability of the integrated intervention, frequency and timeliness of SBDOH intervention, level of challenges of SBDOH in HIV treatment, adherence to ART measured by ID-Cap system, and self-reported medication adherence. Secondary outcomes are plasma HIV viral load and high risk sexual activity,

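### Aim 1 states between-arm hypotheses but names the time coefficient as their test, which does not compare the arms, in a model whose outcome is neither session frequency nor timeliness

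*Protocol article*

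**What the plan says.** The abstract lists these outcomes as primary: "The primary outcomes are acceptability of the integrated intervention, frequency and timeliness of SBDOH intervention, level of challenges of SBDOH in HIV treatment".

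The analysis section for Aim 1 states two comparative hypotheses. On sessions: "the ISS-SBDOH arm will have significantly higher frequency and better timeliness of the SBDOH intervention sessions than the UC arm". On challenges: "the ISS-SBDOH arm will have lower level of challenges of SBDOH over time than the UC arm". It then gives a single method for them: "To test this, we will use GLMM to model the number of challenges of SBDOH over time through parameter estimate of time (fix effect". No arm term and no arm × time term is named.

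The Primary outcome section defines the variables separately. For challenges: "Challenges of SBDOH will be measured as the count of SBDOH issues one is facing, and the degree of each issue". For sessions: "Frequency and timeliness of SBDOH intervention are measured as number of sessions, and time to first, and subsequent sessions, if applicable, from baseline, and others". That section adds that such information is also gathered when the monitoring system triggers an intervention.

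Two other places bear on the point. The sample size section bases power for session frequency, timeliness and level of challenges on a two-sided two-sample t-test with 55 per arm. The limitations paragraph of the Discussion mentions parametric analysis of the time until the first session, without naming a model or an arm contrast.

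**The concern.** The hypotheses ask whether ISS-SBDOH differs from UC. The parameter named to answer them asks whether the number of challenges changes with time. These are different questions and can have opposite answers.

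A shared trend is plausible here. Known SBDOH challenges are one route to eligibility, and both arms can reach the same clinic team, so challenges may fall in both arms whatever the intervention does. An analyst following Aim 1 as written could then report support for a primary hypothesis without having compared the arms. If the arms instead moved in opposite directions, a whole-sample trend would be near zero and a real difference would be missed.

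The named model also has the wrong outcome for half of what it is meant to test: a model of the number of challenges says nothing about how many sessions took place or how soon.

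**Working it through.** **1. What the time coefficient estimates.** Let b_I and b_U be the mean changes per week in ISS-SBDOH and UC. With 1:1 allocation:

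- no arm term: time estimates (b_I + b_U)/2;
- arm and arm × time in the model, UC as reference: time estimates b_U;
- arm × time estimates b_I − b_U.

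The hypothesis on challenges concerns b_I − b_U. Neither version of the time coefficient equals it.

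**2. Comparison with the other aims.** Aim 2 includes an arm dummy to test whether adherence differs between the arms. Aim 3 evaluates an arm × time interaction. Only Aim 1 names time alone.

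**3. The plan's own Aim 1 figure.** The sample size section states 80% power for a 0.5 SD difference with 55 per arm (two-sided 0.05, two-sample t-test). The exact t calculation gives 73.8%; 80% needs 64 per arm. That shortfall is a separate matter and nothing below depends on it. What matters here is that the powered test is a between-arm test and the test named in Aim 1 is not.

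**4. Size, first set of assumptions.** From the protocol: 55 per arm; visits at baseline and weeks 4, 8, 12, 16, 20 and 28. Assumed: continuous outcome with SD 1, constant intra-subject correlation ρ, linear change.

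- Mean visit time 88/7 = 12.57 weeks; S = Σ(t − 12.57)² = 557.7.
- Variance of one participant's fitted slope = (1 − ρ)/S.
- Rejection probability ≈ Φ(|slope|/SE − 1.96).

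Both arms fall by 0.3 SD over 28 weeks (slope 0.3/28 = 0.01071), no arm difference:

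| ρ | SE, 110 participants | Whole-sample time | SE, 55 participants | UC-reference time | arm × time |
|---|---|---|---|---|---|
| 0.3 | 0.00338 | Φ(3.17 − 1.96) = 0.89 | 0.00478 | Φ(2.24 − 1.96) = 0.61 | 0.05 |
| 0.5 | 0.00285 | Φ(3.75 − 1.96) = 0.96 | 0.00404 | Φ(2.65 − 1.96) = 0.76 | 0.05 |
| 0.7 | 0.00221 | Φ(4.85 − 1.96) = 0.998 | 0.00313 | Φ(3.43 − 1.96) = 0.93 | 0.05 |

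Arms diverge by 0.5 SD in total, in equal and opposite directions, ρ = 0.5: slope difference 0.5/28 = 0.01786; SE = √(2 × 0.5/(557.7 × 55)) = 0.00571; arm × time power = Φ(3.13 − 1.96) = 0.88. The whole-sample slope is zero, so time rejects at about 0.05 or slightly less.

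**5. Size, second set of assumptions.** Simulation, 20,000 replicates, random slopes with SD 0.02 per week and residual SD 0.7 (both assumed), same visits and arm sizes:

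| Change over 28 weeks | Whole-sample time | UC-reference time | arm × time |
|---|---|---|---|
| none in either arm | 0.05 | 0.05 | 0.05 |
| both −0.3 | 0.88 | 0.59 | 0.05 |
| both −0.5 | 1.00 | 0.95 | 0.05 |
| ISS −0.3, UC +0.3 | 0.04 | 0.59 | 0.88 |
| ISS −0.6, UC 0 | 0.86 | 0.05 | 0.88 |

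In the last row the intervention works and UC is flat: with UC as reference, the time coefficient rejects only at the nominal rate.

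**6. Outcome of the named model.** It models the number of challenges. Frequency is a number of sessions and timeliness is a time to session; neither is the modelled variable.

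**The case against.** Several points on the other side stand.

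- The text never says that the arms are pooled. It may intend a model with arm in it, and since the hypothesis is comparative, a sympathetic analyst would add the interaction. But under reference coding the time coefficient is still one arm's trend. This lowers the illustrated rejection rate (0.59 rather than 0.88 in one scenario) without making the test an arm comparison. Nor is it detail left to the SAP: the article chose to name the tested parameter.
- A reader might infer that the article has no analysis at all for frequency and timeliness. That goes too far. The sample size section applies a between-arm t-test to them, and the Discussion mentions time to first session. What holds is that the model named in Aim 1 covers neither and agrees with neither of those places.
- A reader might also infer that timing sessions from baseline is an error, and that the clock should start when a need is first recorded. The documents do not support this. Baseline is not the only measure given: the definition is left open to other measures, and information is also collected at triggering. Randomisation follows the baseline assessment, so baseline is a common origin that preserves the randomised comparison. A need first recorded after randomisation could be affected by arm. A need met by a triggered session between visits might be recorded only after that session, giving an undefined time. Where a need exists at baseline, the clock would not change.
- Nor does a participant with no session lack a value: in a time-to-event analysis that participant is censored.
- The rates are illustrative. The trends, correlations and variances are assumed, and a continuous outcome stands in for a count.

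**Conclusion.** Wrong as written. For a primary outcome with a between-arm hypothesis, Aim 1 names a coefficient that does not compare the arms under either reading of the model. Under the assumptions above, a common decline with no arm difference gives about 88% to 100% rejection for a whole-sample time effect and 59% to 95% for a UC-reference one, against about 5% for arm × time. These figures show the scale of the problem and are not estimates of this trial's error rate; the direction follows from the algebra in step 1 and does not depend on the assumed variances. The model named for the session hypotheses has a different outcome from the variables they concern, and the analysis section, the sample size section and the Discussion do not agree on the test.

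**What to change.** In the Aim 1 analysis section:

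1. For level of challenges, replace the time parameter with an arm contrast: arm × time, as in Aim 3, or the arm effect at a stated follow-up week adjusted for the baseline count. Commit to one.
2. For frequency, name a count model for the number of sessions (for example negative binomial with a follow-up offset) with an arm term.
3. For timeliness, name a time-to-event model for time from baseline to first session with an arm term, censoring participants who have no session. Keep baseline as the origin; do not restart the clock at a need recorded after randomisation.
4. Bring the sample size section and the Discussion's remark on time to first session into line with these tests.

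The cost is analysis wording only. The challenge counts, session counts and session times are already to be collected.

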### Study duration

The 16-week intervention phase is long enough to evaluate the acceptability and efficacy of the integrated ISS-SBDOH intervention and fatigue of using ISS [28, 29]. SBDOH treatment sessions may not be able to completely resolve all the adverse SBDOH issues a patient has, but will rapidly start to work out issues With 16-weeks of ID-Cap, the trial will be able to potentially trigger multiple SBDOH intervention sessions for a given participant, and provide rich data to evaluate the effect of the integrated intervention. The 12-week post ID-Cap intervention period is also long enough to detect rapid dissipation of any effects of using the ID-Cap system and the timely intervention on SBDOH triggered by the ID-Cap system. Although there will be no SBDOH intervention triggered by dose missing patterns during this 12-week period, study participants can still get SBDOH interventions through regular clinic visits, provider contacts and/or participant-initiated phone calls.

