### Self-Reported SBDOH needs

In 2013, the Institute of Medicine (IOM) established a committee to develop an initial 25-item questionnaire to measure SBDOH in 2017 [30]. Based IOM’s scale, Menza et al. in 2021 created a 10-item index of SDOH in the context of HIV care outcomes, including missed appointments, adherence, and viral suppression [6]. We will extend this questionnaire by both counts of social determinants and the degree to which the determinants may impact health outcomes (e.g., low/medium/high).

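### Aim 1 tests the level of SBDOH challenges by the number of issues through a time effect, although the primary outcome is number plus degree and the hypothesis compares arms

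*Protocol article*

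**What the plan says.** All references are to the protocol article.

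- **Outcomes, Primary outcome (ii):** "Challenges of SBDOH will be measured as the count of SBDOH issues one is facing, and the degree of each issue". The degree is illustrated as "low/medium/high with housing challenge determined by nurse or care coordinator) with summary scores". Collection is planned at baseline and around weeks 4, 8, 12, 16, 20 and 28.
- **Self-Reported SBDOH needs:** a 10-item index is extended to record both the count and the degree of impact.
- **Statistical analyses, Aim 1:** the hypothesis is that "the ISS-SBDOH arm will have lower level of challenges of SBDOH over time than the UC arm". The test given for it is "we will use GLMM to model the number of challenges of SBDOH over time", and the parameter named is the fixed effect of time.
- **Study duration:** "SBDOH treatment sessions may not be able to completely resolve all the adverse SBDOH issues a patient has, but will rapidly start" to work on them.
- **Discussion, limitations paragraph:** counting, severity categories and time-to-session analyses are listed as methods for capturing variability in the SBDOH measures. None is assigned to a hypothesis.
- **Aims 2 and 3:** Aim 2 names an arm indicator and Aim 3 an arm-by-time interaction.

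**The concern.** The outcome as defined has two components, and the test as written uses one. A count changes only when an issue appears or disappears. A housing problem that moves from high to low is an improvement under the Outcomes definition and no change under the Aim 1 model. Study duration allows for such partial progress within 16 weeks.

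The named parameter is a second difficulty. A fixed effect of time describes change over visits. It does not say whether the intervention arm does better than usual care, which is what the hypothesis asserts.

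At stake is one of the listed primary outcomes. The count, a summary score or a severity category could each be reported as the level of challenges, and the article does not say which of them answers the hypothesis.

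**Working it through.** **1. Definition against test**

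| Element | Outcomes | Aim 1 hypothesis | Aim 1 test |
|---|---|---|---|
| Variable | number and degree, summary scores | level of challenges | number only |
| Contrast | not stated | intervention against usual care | effect of time |

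The variable and the contrast in the last column both differ from what the hypothesis needs. This step needs no assumed figure.

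**2. The plan's own power figure**

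The sample size section gives 80% power for a standardised difference of 0.5 with 55 per arm, two-sided 0.05, t-test.

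- Normal approximation: power = Φ(0.5 × √(55/2) − 1.96) = Φ(2.62 − 1.96) = Φ(0.66) = 74.6%. The exact t-test gives 73.8%.
- 80% power needs 63 per arm (normal) or 64 (t). The detectable difference at 55 per arm is 0.54, which the text may have rounded to 0.5.

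This shortfall is a separate matter. What matters here is that the section refers to a continuous outcome without saying whether that is the count or a score.

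**3. How much the count could lose**

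The documents give no prevalence or expected shift, so the inputs below are assumptions: 10 items, person-specific probability of each issue from Beta(2, 3) (mean 0.4), and degrees 1, 2, 3 equally likely.

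- Count: mean 10 × 0.4 = 4; variance 10 × 2 × 3 × 15 / (25 × 6) = 6; SD 2.449.
- Summed degree: mean 4 × 2 = 8; variance 4 × 2/3 + 2² × 6 = 26.67; SD 5.164.

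Let a fraction q of issues ease one level, and let r be the share of eased low issues that disappear. The count falls by 4qr/3 and the score by 4q(2 + r)/3. The standardised effect on the count, relative to the score, is r/(2 + r) × 5.164/2.449 = 2.108 × r/(2 + r), whatever q is. Power below is at q = 0.5 with 55 per arm.

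| r | Effect kept by count | Power, count | Power, score |
|---|---|---|---|
| 0 | 0% | 5% | 27% |
| 0.25 | 23% | 6% | 33% |
| 0.5 | 42% | 11% | 39% |
| 1 | 70% | 29% | 52% |

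If issues instead resolve outright from any degree, the count falls by 4q and the score by 8q. The ratio is then 2.108 × 1/2 = 1.05, so the count loses nothing.

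**4. Baseline-adjusted simulation**

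Assumptions: 55 per arm, one follow-up, ANCOVA, two-sided 0.05, 2,000 replicates; 10 items each present in 40%, degrees equally likely; in both arms 10% of present issues ease and 10% of items worsen by one level. The intervention acts on an extra 10%, 15% or 20% of present issues.

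| Assumed action | Power, count | Power, summed degree |
|---|---|---|
| Eases one level | 12%, 21%, 35% | 44%, 73%, 92% |
| Eases one level, half of eased low issues vanish | 6%, 10%, 13% | 36%, 68%, 89% |
| Resolves outright | 60%, 90%, 98% | 84%, 98%, 100% |

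Other codings of the same description move these figures. At the 20% one-level shift, the count ranged from 28% to 61% and the score from about 92% to 98%. The score stays ahead in the last row because adjustment removes the spread between persons and the remaining background noise was assumed to be one-level. That too is an assumption.

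**5. Exposure of the score to graded bias**

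Use the same set-up with no true effect, and suppose 10%, 15% or 20% of medium or high issues are graded one level lower in the intervention arm. The summed degree is then significant in 23%, 45% and 67% of trials. The count stays near 5%.

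**The case against.** Four arguments favour leaving the plan as it is.

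- **Degree is still in the plan.** The limitations paragraph commits to severity categories as well as counts, and a condensed article may leave scoring to an analysis plan that is not shown. This stands against any reading that degree has been abandoned. It does not remove the mismatch, because Aim 1 names a variable and it is not the one that Outcomes defines.
- **Partial progress is only a possibility.** A reader might infer that the plan expects issues not to resolve, that the count misses most of any benefit, or that a real effect would probably be reported as null. The documents do not support this. Study duration says "SBDOH treatment sessions may not be able to completely resolve all the adverse SBDOH issues a patient has", which leaves room for some issues to resolve, and each of those lowers the count. The working shows that the loss turns on the assumed mechanism.
- **A count may be the safer variable.** The trial is open-label. The example in Outcomes has degree set by a nurse or care coordinator, and nurses are among the clinic staff who provide the SBDOH service. Low/medium/high grading is more open to expectation than presence or absence. This stands in full, and a change to the score has to disclose it.
- **The time effect may be shorthand.** The authors may intend an interaction, as in Aim 3. That is plausible, but Aims 2 and 3 name an arm term and this sentence does not.

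**Conclusion.** The concern holds in a limited form. The only test stated for the level of challenges covers the count component of a two-component primary outcome, and the parameter it names is not an arm comparison. Both follow from the text alone.

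The count cannot register partial easing, so the test may be less sensitive than the defined outcome. The size of the loss cannot be derived from the documents. It runs from complete, if no issue ever leaves the list, to none, if issues resolve outright. Every power figure in steps 3 to 5 rests on assumed prevalence, degrees, background change and mechanism, and shows direction and range only.

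The point deserves correction because it concerns a primary outcome and the change is cheap. It does not show that the trial will miss an effect.

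**What to change.** In Aim 1, name the summary score already foreseen in Outcomes as the tested variable for the level of challenges, and state how it is formed (for example, absent = 0, low = 1, medium = 2, high = 3, summed). Test it between arms with an arm or arm-by-time term, as in Aim 3. Report the number of issues as a supportive analysis. Align Outcomes, Aim 1 and the limitations paragraph so that all three name the same version, and say in the sample size section which version the continuous-outcome power refers to.

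The cost is wording only, because degree is already to be collected at every scheduled assessment. Two downsides should be stated:

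- **Equal spacing.** A sum treats the steps between low, medium and high as equal. An ordinal analysis can check this.
- **Unblinded grading.** Where available, use the participant-reported degree from the extended questionnaire rather than the staff grade. Participants also know their arm, so this reduces the problem without removing it. Check that the count agrees in direction with the score. A count that does not move is compatible with true partial easing, but one that moves the other way is a warning.
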